### 2.11. The Study Period for Patients

The study period for patients is from 6 January 2020 to 5 March 2021. The time frame includes 60 days of inpatient admission (6 January 2020 to 5 March 2021) and 12 months of follow-up period after hospital discharge).

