### 2.3. Inclusion Criteria (Patients)

Aged 18 years or older.Diagnosed with any mental disorder.Admitted as a psychiatric inpatient for at least 24 h from 6 January 2020 to 5 March 2020.

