### 2.10. Patient-Level Data

From the relevant electronic patient records, we will extract and code (details of how we will code in parentheses) the following variables: Age (age in years at point of hospital admission), gender (coded: 1. Male, 2. Female, 3. Other), employment status at the point of admission (coded: 1. Employed, 2. Unemployed, 3. Student, 4. Retired, 5. Other), primary psychiatric diagnosis (coded: 1. Mood and/or anxiety disorder [including bipolar], 2. Schizophrenia, 3. Personality disorders, 4. Other [specify]), psychiatric comorbidities (coded: 1. Yes, 2. No), substance use (coded: 1. Yes, 2. No), physical comorbidities (coded: 1. Yes, 2. No), date of admission (dd/mm/20yy), detained under mental health law (coded: 1. Yes, 2. No), on a Community Treatment Order prior to admission to hospital (coded: 1. Yes, 2. No), when was the patient discharged from the participating ward? (dd/mm/20yy), Discharged on a Community Treatment Order (coded: 1. Yes, 2. No), admitted by inpatient psychiatric services at the participating hospitals within 12 months of discharge (coded: 1. Yes, 2. No), number of psychiatric admissions during the study period, Health of the National Outcome Scales (HoNOS) total score on admission to hospital, HoNOS total score immediately prior to discharge (recorded as number). Health of the Nation Outcome Scales (HoNOS) is a clinician rated tool comprising 12 simple scales assessing behaviour, impairment, symptoms and social functioning for those in the 18–64 years old age group [20]. We will request the unit managers to extract information on the total number of inpatients on the ward at morning handover (07:00 am) each day between the 6 January 2020 and 5 March 2020 (60 days). The patient data extraction form is available as Supplementary Document (Table S2).

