### 2.12. Nurse-Level Data

#### Roster Data

Roster data will be extracted from CHRIS21 and Kronos for the time period 6 January 2020 through 5 March 2020. System Performance Support [21] defined a roster as a timetable that specifies the number of nurses and their classifications required for each shift. Data on the training nurses have received will be extracted and coded: 1. Mental health nurse, 2. Comprehensive nurse, 3. Enrolled nurse, 4. Nursing assistant, 5. Student nurse. Nurse unit managers will be asked to extract and code data from the shift roster about whether nurses have mental health nursing qualifications. We estimate that data extraction and coding should take no more than four hours of a nurse unit manager’s (NUMs) time. We will check with NUMs during the conduct of the study if the tasks were overly burdensome. We defined a mental health nurse as a registered nurse with a formal educational qualification in mental health nursing. A comprehensive nurse is a registered nurse with a formal educational qualification in general/comprehensive nursing and does not hold a formal mental health nursing qualification. An enrolled nurse is a nurse with a certificate or diploma qualification in nursing and is registered as an enrolled nurse. First level nurse refers to mental health and comprehensive nurses. Second level nurses are enrolled nurses. These data will be entered onto a data extraction form available as Supplementary Document (Table S3).

We will use the total number of nurses working each day as the denominator and then calculate the ratio of 1. Mental health nurse to comprehensive nurse, 2. Registered nurse to enrolled nurse, 3. Qualified nurse to unqualified staff.

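### The 60-day window carries the wrong end year, and roster and ward-census data stop on 5 March 2020 although eligible stays may run past that date

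*Protocol article*

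**What the plan says.** All references are to the protocol article.

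- **Eligibility (Section 2.3):** "Admitted as a psychiatric inpatient for at least 24 h from 6 January 2020 to 5 March 2020". No latest discharge date is given here or elsewhere.
- **Patient study period (Section 2.11):** "The study period for patients is from 6 January 2020 to 5 March 2021". It is then broken down as "60 days of inpatient admission (6 January 2020 to 5 March 2021) and 12 months of follow-up period after hospital discharge".
- **Ward census (Section 2.10):** patient numbers are taken "each day between the 6 January 2020 and 5 March 2020 (60 days").
- **Nurse data (Section 2.12, Roster Data):** "Roster data will be extracted from CHRIS21 and Kronos for the time period 6 January 2020 through 5 March 2020". Nurse eligibility in Section 2.4 has the same end date.
- **Outcome (Section 2.10):** "admitted by inpatient psychiatric services at the participating hospitals within 12 months of discharge (coded: 1. Yes, 2. No"). The clock starts at each patient's own discharge, as it does in the aim (Section 1.6).
- **Exposure (Section 2.25):** nurse and patient counts are formed for each day in hospital and averaged over the admission, with the days of admission as denominator.
- **Inference (Section 2.26):** none is planned, because this is a feasibility study.

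**The concern.** Three sets of dates have to fit together: the admission window, the days on which exposure is recorded, and the period in which readmission is sought. They do not.

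The first fault is a wrong year in the bracket of Section 2.11. The second remains after that is corrected. A patient admitted late in the window may still be in hospital when roster and census data stop, so part of the stay has no exposure data. The same patient's 12 months after discharge end later than the stated end of the study period.

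What is at stake is the feasibility result. Section 2.23 names readmission and nurse education as the two key variables. A gap in either that comes only from the extraction dates could be read as failed linkage or as missing data. The deletion rules in that section could then remove those patients. Whether a patient is affected depends on length of stay, so the loss would not be random. The protocol intends its findings to shape a powered study (Section 5), which could inherit the fault.

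**Working it through.** **1. The stated 60 days.** Inclusive count for 6 January to 5 March 2020 (leap year): 26 days in January + 29 in February + 5 in March = 60. This reproduces the protocol's figure. With the end date printed in the bracket of Section 2.11, a further 365 days are added: 60 + 365 = 425. So 5 March 2020 fits the stated 60 days and 5 March 2021 does not.

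**2. Who gets 12 months by 5 March 2021.** From 5 March 2020 to 5 March 2021 is 365 days. A fixed end on that date gives a full 12 months only to patients discharged on or before 5 March 2020. For a later discharge, the loss equals the days from 5 March 2020 to discharge:

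- discharged 19 March 2020: 365 − 14 = 351 days
- discharged 2 April 2020: 365 − 28 = 337 days

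**3. How many admissions run past 5 March 2020.** The protocol gives no length of stay, so these stays are assumptions, with admissions spread evenly over the 60 days. For a fixed stay of *L* days the share is *L*/60. For exponentially distributed stays with mean *m* it is (*m*/60)(1 − e^(−60/*m*)).

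| Assumed stay (days) | Fixed stay | Exponential stay |
|---|---|---|
| 7 | 7/60 = 11.7% | 11.7% |
| 14 | 14/60 = 23.3% | 23.0% |
| 21 | 21/60 = 35.0% | 33.0% |

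**4. Follow-up lost over all admissions, if 5 March 2021 is a hard end.** In the exponential model the mean remaining stay is *m*, so the lost fraction of 12-month person-time is share × *m*/365:

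- *m* = 7: 0.117 × 7/365 = 0.2%
- *m* = 14: 0.230 × 14/365 = 0.9%
- *m* = 21: 0.330 × 21/365 = 1.9%

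**5. Effect on the skill mix.** Section 2.25 works an example with 8, 9 and 10 comprehensive nurses and 2, 3 and 4 mental health nurses over three days. The ratio of totals is 27/9 = 3, the protocol's figure. The daily ratios are 4, 3 and 2.5, with mean 9.5/3 = 3.17. Now suppose that day 3 falls after 5 March 2020 and has no roster:

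- daily ratios summed and divided by all days of admission: (4 + 3)/3 = 2.33, against 3.17. This is biased down. With a constant daily ratio, a 14-day stay with 7 rostered days is halved (7/14).
- daily ratios averaged over rostered days only: (4 + 3)/2 = 3.5
- ratio of totals over rostered days: 17/5 = 3.4, against 3. The day count cancels here, so there is no automatic downward pull, but the value describes two of the three days.

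On none of these routes is the whole-stay value recovered. A patient admitted on 5 March 2020 has roster data for the first calendar day of the stay only.

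**The case against.** The strongest reply has four parts.

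*The wrong year corrects itself.* The bracket says 60 days and four other sections end on 5 March 2020. This stands: nobody is likely to extract 425 days of admissions. The slip needs correcting, but it carries little weight alone.

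*Section 2.3 may mean stays that lie wholly inside the window.* On that reading the roster covers every stay, and 5 March 2021 is exactly the last possible discharge plus 12 months. The fit suggests that the authors may have had this in mind. But no section states it. The text names an admission of at least 24 hours and sets no discharge limit. If it were intended, stays crossing 5 March 2020 would be excluded, and that would have to be said.

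*The outcome may not be truncated at all.* A reader might infer that late readmissions are bound to be coded No. The document does not support that. Sections 1.6, 2.10 and 2.11 all describe 12 months after discharge, extraction is retrospective, and discharge dates are collected. Miscoding follows only if 5 March 2021 is applied as a hard end of extraction. What stands is that the fixed end and the per-patient definition disagree for late discharges, so one of them must change.

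*No effect estimate is at risk.* This also stands. Sections 2.14 and 2.26 rule out tests of association and inference, so the harm is to descriptive figures and to the judgement of feasibility.

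**Conclusion.** The point holds, at moderate severity.

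- **Certain:** the bracket in Section 2.11 is wrong (425 days against 60).
- **Follows from the text as written:** with no discharge limit, the roster and census end of 5 March 2020 conflicts with whole-stay averaging in Section 2.25 for any patient still in hospital after that date.
- **Conditional:** follow-up shorter than 12 months arises for the same patients only under a hard end on 5 March 2021. The loss is small over all admissions, about 0.2% to 1.9% of person-time for mean stays of 7 to 21 days.

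The share affected, about 12%, 23% or 33–35%, rests on assumed stays of 7, 14 or 21 days and even admissions.

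Two stronger readings should be set aside. A reader might blame the 2021 date for the roster gap; the cause is the separate 5 March 2020 end of the roster and census, and changing the 2021 date would not repair it. A reader might also call the item "number of psychiatric admissions during the study period" an error, because a patient discharged on 7 January 2020 is watched for 423 days afterwards and one discharged on 5 March 2020 for 365. It is a descriptive count over a common calendar period, and the protocol does not present it as a post-discharge outcome.

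**What to change.** 1. In Section 2.11, correct the end of the 60-day window to 5 March 2020.
2. In Section 2.3, state that the index admission date must fall within the window.
3. Run the readmission extract to 12 months after each patient's own discharge, so that it ends at the last index discharge plus 12 months.
4. For exposure, choose one: (a) extend the roster and census extract to the last index discharge; or (b) define the skill-mix average over rostered in-window days only, with those days as the denominator, and report how many stays are truncated.

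**Cost.** The data are retrospective, so this means amended extraction dates. Option (a) adds unit-manager time to the four hours budgeted in Section 2.12, and one long-stay patient sets its length. Option (b) avoids that but leaves a partial-stay exposure for late discharges. Counting admissions over a fixed period after the index discharge would make patients comparable; that change is optional.

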### 2.12. Nurse-Level Data

#### Roster Data

Roster data will be extracted from CHRIS21 and Kronos for the time period 6 January 2020 through 5 March 2020. System Performance Support [21] defined a roster as a timetable that specifies the number of nurses and their classifications required for each shift. Data on the training nurses have received will be extracted and coded: 1. Mental health nurse, 2. Comprehensive nurse, 3. Enrolled nurse, 4. Nursing assistant, 5. Student nurse. Nurse unit managers will be asked to extract and code data from the shift roster about whether nurses have mental health nursing qualifications. We estimate that data extraction and coding should take no more than four hours of a nurse unit manager’s (NUMs) time. We will check with NUMs during the conduct of the study if the tasks were overly burdensome. We defined a mental health nurse as a registered nurse with a formal educational qualification in mental health nursing. A comprehensive nurse is a registered nurse with a formal educational qualification in general/comprehensive nursing and does not hold a formal mental health nursing qualification. An enrolled nurse is a nurse with a certificate or diploma qualification in nursing and is registered as an enrolled nurse. First level nurse refers to mental health and comprehensive nurses. Second level nurses are enrolled nurses. These data will be entered onto a data extraction form available as Supplementary Document (Table S3).

We will use the total number of nurses working each day as the denominator and then calculate the ratio of 1. Mental health nurse to comprehensive nurse, 2. Registered nurse to enrolled nurse, 3. Qualified nurse to unqualified staff.

### 2.13. De-Identifying Data

Identifiable data will not be extracted, for example, the name of the hospital, Unit Record Number (URN) of patients, employee number of nurses, names, addresses, date of birth, phone numbers for both patients and nurses.

### 2.14. Data Storage

Data from participating hospitals will be transferred to the participating University in Victoria through the Cloudstor file transfer. CloudStor is a secure online service that was developed by Australia’s Academic and Research Network (AARNet) that enables universities and the wider community to quickly and securely synchronise, share and store files using the high-speed AARNet network. Data will be stored on a password protected CloudStor and only the researchers will have access. Patient and nurse data will be stored in separate files and then combined to enable analysis.

Following completion of the study, all data collected will be stored by the participating University for seven years following the Public Records Act 1973. We do not intend to make these data available to other researchers because this is a feasibility study, and we do not intend to undertake any formal tests of association.

### 2.15. Disposing of Data

Records stored on Cloudstor will be deleted in line with the current Cloudstor process at the time of destruction.

### 2.16. Ethics Considerations

Permission to conduct the research project was granted by the participating University and two Hospitals’ Human Research Ethics Committees: HREC/70480/Austin-2021 and 2021/SSA00366.

We applied for and were granted a waiver of consent because the study was considered by the ethics committee not likely to cause any discomfort or distress to the participants as we will not directly collect data from them and no identifiable information (e.g., names, hospital numbers, addresses, name of the hospital) will be extracted. The anonymity of the participants can, consequently, be always assured.

### 2.17. Data Management

The following procedure for data management will be followed: Data re-coding and checking, removal of duplicates and unwanted data, management of outliers, checking for consistency, and management of missing data. Stata version 14.0 (Stata Corp., College Station, TX, USA) will be used to execute data management procedures.

### 2.18. Data Recoding

Data will be recoded using the following procedure: A codebook will be created that will contain variable names and numeric codes. A number will be assigned to the label for each variable, for example, for gender, male will be coded 1 and female 2, other 3.

### 2.19. Data Checking

Error in data entry may occur when nurses or psychiatrists make clinical entries into the medical record (for example, at the point of admission to hospital). Common errors in data entry often relate to transposition error, such as: Flipping the last two digits of the year of admission (for example, 16 January 2021 might be entered as 16 January 2120). In this study, we will check for the following potential errors in data entry:○Duplicate and unwanted observations○Outliers○Data consistency○Missing data

### 2.20. Removal of Duplicate and Unwanted Observations

We will check if participants have been entered multiple times in the data. For example, the same admission is entered more than once in the data in error. Where we identify a duplicate entry, we will confirm the entries are duplicates by comparing the patient study identification number and date of admission. If they are the same, we will conclude that an error has occurred. We will retain the entry with most data noting that this may mean that we remove valid observations. However, if the researcher “chooses” which data to retain, this would introduce substantial potential for bias because the researcher might be inclined to retain observation favourable to the primary hypothesis [22].

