### 2.1. Study Setting

Our feasibility study will be conducted in two participating settings, one in South Australia (rural) and the other in Victoria (metropolitan). The site in South Australia is the only rural health care provider in South Australia with a specialised inpatient mental health facility and mental health rehabilitation service. The psychiatric inpatient unit has six beds.

The site in Victoria is a major public health provider in Melbourne. The site has two adult acute inpatient wards and provides a range of community mental health services (for example, mobile outreach service and case management). We chose two sites to test if our study is feasible in different states of Australia as well as in rural and metropolitan areas.

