### 2.21. Outliers

Outliers are extreme values that are well outside the overall pattern of a distribution of variables leading to under- or overestimation of the true mean. A potentially important source of bias, it is important to consider in advance how these will be managed in the analysis of the data set [23]. To identify outliers, we will use box plots. Box plots are considered most suitable for exploring both symmetric and skewed data. Infrequent values in categorical data can also be identified using the box plot [23].

There are two main procedures for managing outliers: First, we will go back to the data and check the original value entered. If the extracted number is incorrect, we will amend our database accordingly, documenting any changes that have been made. Second, if the source and extracted data match but the value is seemingly impossible (e.g., the participant was 150 years of age), we will delete the data and consider the value as missing in the analysis.

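### The duplicate rule keeps the fuller of two entries with no merge and no source check, so it can discard valid fields and settle conflicting values by completeness

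*Protocol article*

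**What the plan says.** Section 2.20 of the protocol article deals with admissions that appear more than once in the extract.

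- **Test for a duplicate:** "we will confirm the entries are duplicates by comparing the patient study identification number and date of admission".
- **Conclusion when these agree:** "If they are the same, we will conclude that an error has occurred".
- **Action:** "We will retain the entry with most data noting that this may mean that we remove valid observations".
- **Reason:** if the researcher were to pick the entry to keep, "this would introduce substantial potential for bias because the researcher might be inclined to retain observation favourable to the primary hypothesis".

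The section has no step for combining two entries, no step for entries whose filled values differ, and no check against the hospital record.

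Section 2.21, on outliers, takes another route: "First, we will go back to the data and check the original value entered". Wrong values are then corrected and the change documented. A value that matches the source but is impossible is set to missing.

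**The concern.** Completeness and correctness are different properties. A rule that ranks entries by how many fields are filled has two weaknesses. It throws away whatever only the sparser entry holds, and it gives no protection against an error in the fuller entry. The article concedes the first and does not discuss the second.

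The aim of the study is to show whether patient and nurse data can be extracted and linked well enough to support a later powered study. How complete the data are is therefore one of its main products. A cleaning step that removes recorded values makes the source systems look less complete than they are. Readmission within 12 months is one of the two key variables in section 2.23, so losing it from a patient's record matters more than losing a background field. A weak rule could also be carried into the powered study.

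**Working it through.** The plan states no figure for duplicates, so there is nothing to reproduce. The check sets the sections side by side and follows the rule through the cases it can meet.

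**Inputs**
- Matching key: study ID and admission date (section 2.20).
- Entry kept: the one with more data (section 2.20).
- Fields that could differ: among others, ward discharge date, readmission within 12 months, and the two HoNOS scores (section 2.10).
- Key variables: readmission and nurses' educational preparation (section 2.23).
- Expected errors: section 2.19 gives mistyped dates as a common error.

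**Cases for two entries that share ID and admission date**
1. *Identical entries.* Dropping either is harmless.
2. *One entry's filled fields are a subset of the other's, with no disagreement.* Keeping the fuller entry loses nothing.
3. *Each entry holds a field the other lacks.* The field held only by the sparser entry is lost, although it is valid. If that field is readmission, a known outcome becomes missing. Section 2.23 then deletes the patient listwise if the missingness is judged completely at random or not at random, and imputes the value if it is judged at random. In either case a value that was on file is not used.
4. *Both entries are filled but disagree.* The fuller entry wins. Suppose its discharge date is mistyped and the sparser entry's is right: the wrong date is kept, and with it the wrong number of days of admission, which is the denominator of the averaged skill mix in section 2.25.
5. *The entries are equally complete and disagree.* The rule gives no answer, so someone must choose, which is what the rule was meant to prevent.

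The rule is sound in cases 1 and 2, lossy in case 3, unreliable in case 4 and silent in case 5.

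**Does the stated reason require the rule?** The reason is to exclude researcher choice. Filling gaps from the other entry and sending conflicts to source, with unresolved values set to missing, can be fixed in advance and leaves nothing to choose. It meets the same aim without the losses in cases 3 to 5.

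**Consistency with section 2.21.** An implausible single value is traced to source and corrected with documentation. Two contradictory values for the same field are at least as clear a sign of error, yet no tracing is named for them.

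**The case against.** **The rule is prespecified, its cost is disclosed and a reason is given.** This stands as far as it goes: the authors do not hide that valid observations may go. But the reason supports having a fixed rule, not this one in particular.

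**The rule is aimed at admissions entered twice by mistake, and the fuller entry is the one kept.** Also true. The loss is confined to fields held only in the sparser entry and to correct values that conflict with the fuller one. With no inference planned (section 2.26), the consequences are small.

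**Merge detail usually belongs in a fuller data-management document.** That would answer a silence. Here the article states the rule and its outcome.

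**A stronger reading that a reader might infer.** At the Victorian site, "The site has two adult acute inpatient wards", and the discharge item asks "when was the patient discharged from the participating ward". From this one might conclude that a patient moved between wards has two true rows and that the rule deletes one segment of the stay. The documents do not support that as a fact. They do not say that the extract has one row per ward segment, that such rows would share an admission date, or that transfers occur. Sections 2.24 and 2.25 describe a patient-level data set with one row per patient, and section 2.10 lists no ward identifier.

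Nor can a size be put on it. Take an assumed 14-day stay of 8 days on one ward and 6 on the other. If both rows carry the hospital admission date, the later row runs from day 1 to day 14. Keeping it loses 0/14 = 0% of days, with only ward attribution in doubt; keeping the earlier row loses 6/14 = 43%. A loss of 8/14 = 57% would need the second row to begin at transfer, but its admission date would then differ and the rule would not apply. These figures rest wholly on the assumption and are not an estimate for this study.

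**Conclusion.** The point holds for the rule as written. It declares an error on two fields, discards valid values held only in the dropped entry, and resolves contradictions by completeness without the source check that the next section prescribes for outliers. Avoiding researcher choice does not require this.

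No magnitude can be derived, because the article gives neither the expected number of duplicates nor how often they would disagree. The effect is confined to descriptive and completeness results. Loss or misattribution of a ward segment at the Victorian site is a possible consequence that depends on how its extract is built; the South Australian site is described with a single inpatient unit. This is a cheap improvement to data handling and does not threaten the study's conclusions.

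**What to change.** Revise section 2.20 as follows.

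1. Treat agreement on study ID and admission date as a flag for a possible duplicate, not as proof of error.
2. Where a field is filled in only one of the flagged entries, carry that value into the retained record.
3. Where filled values conflict, including discharge date and ward if it is recorded, ask the site to check the source as in section 2.21. Correct and document the value, or set it to missing if it cannot be resolved.
4. If the source shows that the entries are ward segments of one admission, retain both as one stay.
5. Report the number of flagged duplicates and of conflicts by site, as a feasibility result.

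Discharge date should not be added to the matching key so that any disagreement makes the rows separate segments. A true duplicate with one mistyped discharge date would then be joined as a false segment, and section 2.19 warns of such date errors. A disagreement should lead to a source check.

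The cost is a few lines of protocol wording and Stata code, plus a small number of source checks. The site must make these checks, because section 2.13 keeps hospital record numbers out of the extract.
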